## Methods

### Study Setting

The study will be conducted in Malema, Mecuburi, and Lalaua districts in Nampula Province, northeastern Mozambique (Figures 1 and 2). Several key informant interviews may be conducted with stakeholders based in Maputo.

To identify suitable districts for SMC, an SMC suitability ranking was conducted by the WHO for all provinces. These criteria included a variety of factors such as (1) seasonality eligible for SMC (60% of rainfall concentrated in 4 months), (2) mortality (areas of highest under-five mortality using health management information system) data, (3) access to care (highest ranking given to areas where access to care was poor), and (4) treatment-seeking behavior (highest ranking given to areas where treatment-seeking behavior was poor). Using these four main categories, the average will be calculated to estimate the final ranking and identify the top 20 suitable districts to maximize the impact of SMC. From the list of suitable districts, an additional consideration was taken given the importance of implementing the intervention in an area where no other new interventions were taking place so that an evaluation could be implemented aiming at attributing change to the intervention under investigation. Hence, Malema and Mecuburi districts in Nampula Province were selected, with Lalaua as a comparator, as no indoor residual spraying or new long-lasting insecticidal nets were targeted in these areas, ensuring a robust evaluation component for this pilot study.

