#### Primary Outcome

The primary outcome of this study will be visits to a health facility for suspected malaria by eligible children and confirmation of malaria diagnosis using an RDT during the 5-month study period, which includes a period of 28 days after the final administration of SPAQ.

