#### Recruitment and Data Collection

Households will be randomly sampled from selected communities in both the control and intervention arms and 1 eligible child recruited at random in each household. A short baseline questionnaire will be administered to collect individual data on each child and to confirm their eligibility after the caregivers provided their consent. In the intervention arm, the questionnaire will be administered before the intake of SPAQ for SMC. The primary end point will be recorded through passive surveillance by study clinicians in both the intervention and comparator areas during the 4-month study period. Children recruited into the study presenting at clinics will be identified using information on SMC record cards, on which a child’s information and SMC doses are recorded, and data on health facility visits including suspected malaria cases and results of RDTs will be matched to baseline questionnaire data to build a database for analysis.

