#### Data Analysis

Data will be analyzed using multivariate logistic regression with odds ratios estimated for the association between allocation to the intervention arm and (suspected and confirmed) malaria diagnosis at any point during the study period, converted to a percentage estimate of protective effect. To compensate for the lack of preintervention random allocation of participants to intervention or control groups, covariate adjustment will be made for potential confounders that may influence respondents’ odds of experiencing a clinically significant case of malaria. Covariates, measured at baseline, will include sex, age, parental education, and long-lasting insecticidal net use and all of these will be operationalized as categorical variables. Analyses will also use a multivariate Cox proportional hazards model with multiple Cox regression. *Failure* defined as a visit to a health facility for suspected malaria and/or a confirmed case of malaria and timing of this event based on the original date of health facility attendance during the study period and the estimated protective effect calculated.

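### The trial's named covariates leave out access to care and treatment seeking, although the primary outcome counts only malaria brought to a health facility

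*Protocol article*

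**What the plan says.** The following all come from the protocol article.

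- **Allocation.** The Overview of the Nonrandomized Controlled Trial sets up two arms: one in the comparator district, the other in one of the two SMC districts. Communities and children are sampled at random within districts, but treatment follows the district.
- **Outcome.** Under Primary Outcome, the endpoint is "visits to a health facility for suspected malaria by eligible children and confirmation of malaria diagnosis using an RDT".
- **Ascertainment.** Under Recruitment and Data Collection: "The primary end point will be recorded through passive surveillance by study clinicians in both the intervention and comparator areas". No active case detection is described for this component.
- **Adjustment.** Under Data Analysis, to compensate for the absence of random allocation, "covariate adjustment will be made for potential confounders that may influence respondents’ odds of experiencing a clinically significant case of malaria". The covariates, all measured at baseline and made categorical, "will include sex, age, parental education, and long-lasting insecticidal net use". The main result is an odds ratio from logistic regression, converted to a percentage protective effect. A Cox model is also planned, in which a visit for suspected malaria can count as failure.
- **Baseline data.** "A short baseline questionnaire will be administered to collect individual data on each child". The article does not list the questionnaire's other items.
- **District ranking.** Study Setting lists four criteria for ranking areas for SMC. Two of them are "access to care (highest ranking given to areas where access to care was poor") and "treatment-seeking behavior (highest ranking given to areas where treatment-seeking behavior was poor"). The other two are seasonality and under-five mortality.

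**The concern.** The outcome is the product of two things: having a malaria episode, and bringing it to a facility where it is tested and recorded. SPAQ is meant to act on the first. Distance, access and care-seeking habits act on the second. If the share of episodes brought to care differs between the two districts, that difference enters the estimate as though it were a drug effect, in either direction.

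With one district per arm, local differences cannot average out across districts, so the regression model carries the whole burden within this component. Sex, age and net use say little about whether a sick child reaches a facility; parental education is at best a partial proxy. The Cox analysis is at least as exposed, because its failure definition can be met by a visit for suspected malaria.

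Access and treatment seeking are not obscure candidates: the protocol uses both to separate areas when ranking them for SMC. The set also contains no measure of the child's malaria risk before cycle 1, which is a reasonable adjustment variable in any nonrandomized comparison.

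**Working it through.** **Step 1. Reproduce the plan's own figure.** Sample Size gives a control risk of 0.20, a 40% reduction (hence 0.12 under SMC), 80% power and 5% significance (two-sided assumed).

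- Unpooled variance: n per arm = (1.96 + 0.8416)² × (0.20 × 0.80 + 0.12 × 0.88) / 0.08² = 7.849 × 0.2656 / 0.0064 ≈ 326. Pooled variance gives 329. The stated 327 is reproduced.
- Loss to follow-up: 654 / 0.80 = 817.5, so 818, as stated.
- The recruitment target of 400 per arm less 20% leaves 320 per arm. Expected events: 320 × (0.20 + 0.12) ≈ 102.

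The sample-size arithmetic is therefore not at issue.

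**Step 2. Effect of unequal presentation on the estimate.** The 0.20 is already the risk of a facility-presenting episode. Let r be the share of episodes reaching care in the SMC district divided by the share in the control district. Then the observed risk in the SMC arm is 0.20 × (1 − true reduction) × r, and the apparent protection is 1 − OR, with control odds 0.20 / 0.80 = 0.25. The shares of 50%, 60% and 70% are assumptions; the protocol gives none.

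| Share reaching care, SMC vs control | True risk reduction | Observed SMC risk | OR | Apparent protection |
|---|---|---|---|---|
| equal | none | 0.200 | 1.00 | 0% |
| equal | 40% | 0.120 | 0.545 | 45% |
| 50% vs 60% | none | 0.167 | 0.200 / 0.25 = 0.80 | 20% |
| 50% vs 60% | 40% | 0.100 | 0.111 / 0.25 = 0.44 | 56% |
| 70% vs 60% | none | 0.233 | 0.304 / 0.25 = 1.22 | -22% |
| 70% vs 60% | 40% | 0.140 | 0.163 / 0.25 = 0.65 | 35% |

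On the odds-ratio scale a true 40% risk reduction shows as 45% even with no bias. The distortion is therefore from 45% to 56% or 35%, and from 0% to 20% or -22%. On the risk scale the same four biased cases would read 17%, 50%, -17% and 30%; the odds-ratio figures are the relevant ones because that is what the plan converts.

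**Step 3. Effect on the test, 320 per arm, two-sided 5%.** Again r is assumed.

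- No drug effect: r = 0.9 gives a rejection rate of about 10%; r = 0.8 about 26%; r = 0.7 about 52%. For r = 0.8: difference 0.04, null standard error √(0.18 × 0.82 × 2 / 320) = 0.0304, alternative standard error √((0.16 + 0.1344) / 320) = 0.0303, so Φ((0.04 − 1.96 × 0.0304) / 0.0303) ≈ 0.26.
- True 40% reduction: power is 79% at r = 1 and falls to 38% at r = 1.25, where the observed risks are 0.20 and 0.15.

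These are unadjusted calculations. They would carry over to the adjusted model to the extent that the four named covariates fail to capture the difference in presentation.

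**The case against.** **The protocol does not say that the trial districts differ.** A reader might infer from Study Setting that the plan itself regards the intervention and comparator districts as unequal in access, treatment seeking and previous malaria. It does not. The ranking is of areas in general, no values are given for Malema, Mecuburi or Lalaua, and the stated reason for choosing them is that no spraying or new nets were targeted there. The molecular marker section calls the comparator a neighboring district with similar epidemiology, although that sentence belongs to another component and does not mention access. Previous malaria is neither a ranking criterion nor described as differing anywhere. All of this stands. What remains is that the protocol recognizes access and treatment seeking as varying between areas and names neither as a covariate.

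**The list may not be complete.** The wording is not exclusive, the article condenses a fuller protocol, and the questionnaire is not shown. That limits certainty about what is collected. But the article does fix a covariate list for this analysis, and no further covariate is named.

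**Other components help.** The routine-data analysis uses an age discontinuity, so a difference in access that affects all ages alike would not appear there as an SMC effect. That is a real strength of the overall study, but it does not repair the trial's own estimate.

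**Adjustment cannot solve a design with one district per arm.** Correct for anything that is constant within a district. Travel time and usual care seeking vary between households, so adjusting for them removes part of the bias, not all of it.

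**Conclusion.** The point holds as an omission from the named adjustment set. The outcome depends on attendance, ascertainment is passive, allocation is one district per arm, and neither access to care nor treatment seeking is adjusted for. The absence of a baseline malaria-risk measure is a secondary criticism, made on general grounds.

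The documents do not show that bias is present, nor in which direction. The size depends entirely on an unknown ratio of presentation between districts. Under the assumed 10-percentage-point differences around 60%, and control risk 0.20, the apparent effect of a useless drug ranges from about -22% to 20%, and that of a true 40% risk reduction from about 35% to 56%, against 45% with no difference in presentation. These figures assume that the named covariates absorb none of the difference.

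This is an inexpensive improvement worth making. It is not an error that invalidates the trial.

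**What to change.** 1. Add to the baseline questionnaire: travel time or distance to the nearest health facility, place of care for the child's last fever, and fever or malaria in a defined period before cycle 1. Ask them identically in both arms.
2. Name these as covariates in both the logistic and the Cox models, alongside the four already listed.
3. The article reports that data collection began in October 2020. If the questionnaire is closed, derive the distance from each sampled community to its facility and adjust for that.
4. Optionally, add facility-level malaria incidence before November 2020, where it varies within a district. This is additional extraction, since the planned register listings begin in November 2020.
5. State in the limitations that, with one district per arm, adjustment reduces but cannot remove confounding by district.

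The cost of the first two items is a few questions at the enrollment interview and a few degrees of freedom, which about 102 expected events can support.

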### Assessment of SMC Distribution Impact on Reported Malaria Morbidity Indicators Using Routine Data

We will investigate the impact of SMC on reported malaria morbidity (as a primary end point) in children aged 3-59 months in the study area. Differences in rates of malaria incidence by age at the health facility level will be investigated using a quasi-experimental design based on regression discontinuity analysis, taking advantage of the discontinuity in eligibility for SMC based on age.

Before obtaining data on malaria indicators at the health facility and district levels, a data quality audit will be conducted to assess the quality of the data that will be used for analysis. The quality of data from districts where SMC is implemented will also be compared with that of data from the comparator district. Health management information system data on health facility attendance for children aged 0-13 years (inclusive) will be extracted from health facility registers as full line listings, covering November 2020 to May 2021 in both implementation districts and the control district by photographing the relevant pages of the registers and entering data directly into Excel tables as appropriate. While monthly suspected malaria cases presenting at each health facility will be calculated, other variables including date of health facility attendance, sex, date of birth (or closest estimate of age in months as a preference, or age in years if this cannot be confirmed from an identity document, previous health facility record, or vaccination or medical card), whether a malaria test was performed, the type of test performed (RDT or microscopy), test results (confirmed malaria or negative test results), malaria mortality, and any other variables collected routinely for all child attendees (eg, nutrition status) will be obtained. Observations from registers will be categorized by children’s ages according to the smallest possible increments. Incidence curves [34] for suspected and confirmed malaria cases by age will be modeled from these data (using offset terms to adjust for estimated numbers of children in each age category by health facility catchment area). Incidence curves by age will either be fitted with quadratic or cubic regression terms in Stata 16 (StataCorp) or using a thin plate spline term in R (R Foundation for Statistical Computing; using the mixed gam computation vehicle package). Regression discontinuity analysis [35] using negative binomial models will then be used to assess the reduction in malaria incidence by age-dependent eligibility for SMC. As the primary exposure variable, eligibility will be coded as a binary variable (1=3-59 months 0=0-2 months and 60-155 months) based on age at the start of the SMC round and district. Adjustments will be made for the month of health facility attendance. If possible, random effects will be fitted, with observations of monthly malaria cases nested within clinics. The results will be expressed as rate ratios for the difference in incidence in the eligible age group compared with the expected incidence curve. Models will adjust for sex as an interaction term (considered a moderator for age-dependent malaria susceptibility). Sensitivity analyses may consider the effects of unintended coverage of children aged 5-9 years.

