### Study Populations

The study population that is eligible to receive SMC includes afebrile children of either sex, aged 3-59 months, for any of the SMC cycles, residing in Malema and Mecuburi districts. In addition, for the purpose of the end-of-round survey, which includes an indicator measuring the age eligibility of enrolled children, we included children residing in the aforementioned districts, aged 5-10 years, who may inadvertently have received SMC. In addition, health workers who are involved in SMC implementation, caregivers of children aged under 10 years, community leaders, and key stakeholders such as health officials at different levels of the health system and those involved in SMC implementation will be sampled, according to the study objective, described in more detail in the *Methods* section. The Lalaua district will serve as a control area (see Table 1 for estimated population sizes).

**Table 1 table1:** Estimated target population of seasonal malaria chemoprevention implementation districts and comparison district by age (2020).

Target population estimates		Population of children aged 3-11 months, n (%)	Population of children aged 12-59 months, n (%)	Total population, n	

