### Study Design

We will adopt a type 2 hybrid effectiveness-implementation study design that evaluates the effects of a clinical intervention on relevant outcomes while collecting information on implementation [29]. The hybrid effectiveness-implementation study design supports the pursuit of different lines of research simultaneously, which facilitates the more rapid translation and uptake of study findings for policy makers and implementers [29,30]. This study will use mixed methods to address the aforementioned objectives. Assessments of the protective effect of SPAQ, as delivered as part of SMC implementation, will provide evidence on whether this is appropriate in a region where SP resistance is suspected. Evaluating the implementation of SMC will generate knowledge on the feasibility and acceptability of this intervention in situ, including the challenges, barriers, and facilitators in the local context. Such findings can be useful to inform which intervention components are generalizable and which require local adaptation for other settings [31].

Four monthly cycles of SMC drugs will be distributed door-to-door to eligible children aged between 3 and 59 months by community distributors between November 2020 and February 2021 in 2 districts of Nampula Province. SMC tools and protocols used in Sahelian countries where the Malaria Consortium supports SMC delivery will be adapted to the context in Mozambique for this purpose. A third district will serve as a comparison district (the latter will receive standard malaria prevention, control, and case management). Data collection across the study components was conducted between October 2020 and May 2021 (Figure 3).

The methods are organized according to the study objective, described in more detail below, with an overview provided in Table 2 and Figure 3.

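### Routine-data analysis: eligibility coded once at the start of the round misplaces infants who age into SMC and, if follow-up runs to May, dilutes the rate ratio with post-protection months

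*Protocol article*

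**What the plan says.** The section on reported malaria morbidity from routine data sets the primary exposure: eligibility is "coded as a binary variable (1=3-59 months 0=0-2 months and 60-155 months) based on age at the start of the SMC round", combined with district. Register data are taken as line listings "covering November 2020 to May 2021 in both implementation districts and the control district". The model adjusts for month of attendance and reports a rate ratio for the eligible ages against the expected incidence curve by age. The only sensitivity analysis named concerns unintended coverage of children aged 5-9 years.

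Other sections bear on this rule:

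- Study Populations describes those who may receive SMC as children "aged 3-59 months, for any of the SMC cycles".
- Study Design places the four monthly cycles "by community distributors between November 2020 and February 2021 in 2 districts of Nampula Province".
- The primary outcome of the nonrandomized trial uses a 5-month period "which includes a period of 28 days after the final administration of SPAQ".
- Table 2 gives two time frames for the routine-data component. The study-population column lets the morbidity analysis end in March or in May 2021, while the inclusion column gives May only.

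**The concern.** The design draws its information from the change in eligibility at 3 and 60 months of age. A code fixed at the start of the round does not follow the infants who reach 3 months while SMC is being given. They can be treated, yet they remain in the unexposed group next to the lower cut-off. Infants born after the start have no age at the start, so the rule does not place them at all.

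The code also does not change after protection ends. If attendances to May are analysed, children coded 1 contribute months in which, by the window the protocol uses for its own trial, they are no longer covered. A main effect of month shifts the incidence of all children together. It cannot let the eligibility effect differ between protected and unprotected months.

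Both errors pull the rate ratio toward 1. Reported morbidity is the primary end point of this component, and the pilot is run where SP resistance is suspected, so dilution could be mistaken for weak protection.

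**Working it through.** The routine-data component states no sample size, power or expected effect beyond its 26 health facilities, so there is no figure of the plan's to reproduce.

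**Inputs**

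- Four monthly cycles, November to February (Study Design).
- Register months November to May, 7 in all (routine-data section).
- Window of 28 days after the last administration, taken here as cover to the end of March, that is 5 months (Primary Outcome of the nonrandomized trial).
- Illustrative true rate ratios: 0.60, borrowed from the 40% reduction in the trial's sample size section, and 0.25, from the 75% reduction quoted in the Introduction.
- Assumptions not in the document: full coverage, incidence flat by age, and the share of cases in April-May.

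**1. Ageing-in at 3 months**

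Age in months at cycle 1, and the cycles at which the child has reached 3 months:

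- age 2: cycles 2, 3, 4 (3 child-cycles)
- age 1: cycles 3, 4 (2 child-cycles)
- age 0: cycle 4 (1 child-cycle)

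The total is 6 of 3 × 4 = 12 child-cycles, all coded 0.

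Relative incidence in this group over November-February, for a true rate ratio of 0.60: (6 × 0.60 + 6)/12 = 0.80. The apparent ratio against this group alone is 0.60/0.80 = 0.75. For a true 0.25: (6 × 0.25 + 6)/12 = 0.625, and 0.25/0.625 = 0.40.

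In a pooled comparison the group is 3 of 99 one-month age bands (3 bands at 0-2 months plus 96 at 60-155 months). Reference incidence is (3 × 0.80 + 96)/99 = 0.9939, and 0.60/0.9939 = 0.604. For a true 0.25 the pooled figure is 0.253.

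**2. Months after protection**

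Let w be the share of the cases expected *without SMC* that fall in April-May. With no effect in those months:

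observed RR = w + (1 − w) × true RR

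| w | true 0.60 | true 0.25 |
|---|---|---|
| 0.15 | 0.15 + 0.85 × 0.60 = 0.66 | 0.36 |
| 2/7 (flat incidence) | 0.286 + 0.714 × 0.60 = 0.71 | 0.46 |
| 0.35 | 0.35 + 0.65 × 0.60 = 0.74 | 0.51 |

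A true protection of 40% would thus read as 34% to 26%. If only 4 of the 7 months are protected (for example, the last cycle early in February), flat incidence gives 3/7 + 4/7 × 0.60 = 0.77.

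If the analysis stops in March, w = 0 in this formula and nearly all of the dilution disappears.

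**The case against.** **The end in May is not settled.** November to May is the extraction window, and Table 2 allows the analysis to end in March. A reader might infer that the plan definitely applies the exposure through May. It does not: two places point to May and one leaves March open. The dilution is therefore conditional, and the open end date is part of the point.

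**The dilution is not a forecast.** A reader might take 29% protection instead of 40% as the expected loss. That figure needs w = 2/7 of counterfactual cases, hence flat incidence, although the districts were ranked partly on rainfall concentrated in 4 months. If 2/7 were instead the share of *observed* cases among eligible children, w would be 1.2/6.2 = 0.19 and the ratio 0.68. Only the range, labelled as assumed, is supportable.

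**Ageing-in is small overall.** Six of 12 is a count of child-cycles, not a bias. The pooled shift of about 0.004 confirms that the harm is confined to the lower cut-off.

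**The 60-month edge.** A reader might infer that children aged 57-59 months at the start are also miscoded. The text does not say that a child loses eligibility on turning 60 months during the round, and assignment by age at the start is a defensible intention-to-treat style rule. Even on a per-cycle reading it concerns 6 of 57 × 4 = 228 child-cycles.

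**The upper age limit.** A reader might also see a gap between extraction to age 13 and coding to 155 months. The code uses age at the start, so a child of 155 months in November is about 161 months, and 13 years old, in May. This is not a defect.

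**Scope.** Whether SPAQ protects is addressed more directly by the nonrandomized trial. The 28-day window belongs to that component, and eligibility is a valid programme-level exposure. The article is condensed, so a fuller protocol may contain period restrictions. What stands is that the coding rule is stated outright, does not fit the per-cycle eligibility described in Study Populations, and comes with an inconsistent end date.

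**Conclusion.** The point holds in limited form. The stated code leaves infants who age in as unexposed at the 3-month cut-off and leaves infants born during the round unplaced. That error matters locally (a true 0.60 could read as 0.75 against this group alone, with full coverage and flat incidence) and is negligible in a pooled ratio.

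The larger effect depends on the end date. If the analysis runs to May with only a month main effect, a true 0.60 would read as about 0.66-0.74, assuming that 15-35% of the cases expected without SMC fall in April-May and that protection ends in March. The document gives neither the monthly distribution nor achieved coverage, so these are ranges and not estimates. Both errors act toward no effect, and the named sensitivity analysis covers neither.

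**What to change.** - Reconcile March and May between Table 2 and the routine-data section before analysis.
- Take the primary estimate over November to March, ending 28 days after the last cycle, or fit an eligibility-by-period interaction. Report April-May separately as a post-protection comparison period. Do not recode it as unexposed, since that would put recently treated children in the reference group.
- At the lower cut-off, update eligibility by age at the most recent cycle, with infants not yet born at that cycle coded 0. Alternatively, exclude attendances by children aged 0-2 months at the start once they reach 3 months, and state how infants born later are placed.
- At 60 months, keep assignment by age at the start, with age at each cycle as a sensitivity analysis.

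The cost is mainly recoding: attendance date, date of birth or age, and district are already extracted. The population offsets must follow the same age coding. The primary window is shorter, with fewer cases, and children whose age is recorded only in years need a sensitivity analysis near the cut-offs.
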